#### **6.1.2 Opioids Craving Visual Analog Scale**

The other primary outcome is the opioid craving using a visual analog scale for drug craving marking on a 100-millimetre line in proportion to their craving from 0 (no craving) to 100 (strong craving)[50]. The degree of craving will be marked by subjects at baseline, the 2nd, the 4th, the 6th, and the 8th week after acupuncture administration and at the post-treatment follow-up visits in the 12th, the 16th, and the 20th week. The minimal clinically important difference (MCID) for the opioid craving VAS is 4.0 points [51,52].

### **6.2 Secondary Outcomes**

#### **6.2.1 Clinical Opioid Withdrawal Scale (COWS)**

Opioid withdrawal symptoms will be assessed using the Chinese version of the

COWS [53] from baseline to the 2nd, the 4th, the 6th, and the 8th week after acupuncture administration and at post-treatment follow-up visits in the 12th, the 16th, and the 20th week. COWS evaluates common signs and symptoms of opioid withdrawal and monitors these symptoms over time. The scale consists of 11 items, including heart rate, gastrointestinal discomfort, sweating, tremor, yawning and other symptoms related to opioid withdrawal. Each item has 4 options, and the mark can best describe the root symptoms or signs of the subject option. The total score of 11 items is calculated: 5-12 scores represent mild, 13-24 moderate, 25-36 serious, and above 36 severe withdrawal symptoms.

### **6.2.2 Pittsburgh Sleep Quality Index (PSQI)**

Sleep quality will be assessed using the Chinese version of the PSQI[54] from baseline to the 4th, the 8th, the 12th, the 16th and the 20th week. The Chinese version of PSQI has demonstrated reliability and validity similar to that of the original language version [55]. PSQI evaluates sleep disturbances through subjective sleep quality, sleep duration, sleep latency, habitual sleep efficiency, sleep disturbances, daytime dysfunction and use of sleeping medication. Each item is graded on 4-point (0–3), which is summed together and gains a total score (0 to 21). Higher scores show that patients suffer severity of sleep disturbance and a total score higher than 5 indicates “poor sleep”.

### **6.2.3 The Beck Depression Inventory-II (BDI-II)**

BDI-II, a self-reported questionnaire, will be used to assess the severity of depression, which consists of 21 symptoms [56]. Each symptom is graded on 4-point (0–3), which is summed together to yield a total score (0 to 63). Higher scores mean greater severity of depression. The Chinese version has been validated in adolescents[57]. The BDI-II will be assessed at baseline, the 4th, the 8th, the 12th, the 16th, and the 20th week.

### **6.2.4 The Beck Anxiety Inventory (BAI)**

Anxiety symptoms will be assessed by the BAI, which is a questionnaire with 21

items [58]. Each symptoms rate is on a 4-point (0-3). The maximum score is 63 and higher scores indicate greater severity of anxiety. The BAI will be assessed at baseline, the 4th, the 8th, the 12th, the 16th, and the 20th week.

Independent research assistants will supervise patients to complete the opioid craving VAS and all secondary outcome measures in pen and paper format and evaluated their outcomes.

## **7. Urine Test**

All participants will be asked to submit a urine sample at baseline, and randomly during the study each month, which are used to test for opioid use.

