### **3 Study Design and Methods**

#### **3.1 Study Design**

This is a parallel-arm, patient-blinded, multicenter, randomized, controlled trial. All eligible individuals will be randomly assigned to the manual acupuncture group or the sham control group through central randomization in a 1: 1 ratio. The time period of this trial consists of one week of baseline assessment, 8 weeks treatment period following randomization and a follow-up period of an additional 12 weeks post-treatment. The study flowchart of study procedure is presented in **Figure 1**.

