#### **3.2 Randomization, Allocation, and Blinding**

Eligible patients are randomly assigned in an equal ratio to the manual acupuncture group or the sham control group via a central randomization system designed by the Clinical Research and Big Data Laboratory, South China Research Center for Acupuncture and Moxibustion, Guangzhou University of Chinese Medicine (<http://47.119.117.255/>). The randomization sequence is generated in the block size of 4. Participants will be informed that they have an equal chance to be assigned to the manual acupuncture group or the sham control group. After participants sign the informed consent form and complete baseline assessments, the researcher applies for the randomization number and allocates participants to each group. Allocation of participants is performed by an independent researcher at the clinical site who is not involved in the outcome assessment. Due to the nature of this study, acupuncturists are not blinded to group allocation. However, the outcome assessors, physicians who prescribe patient's methadone, national government personnel who is responsible for recording daily consumption of methadone, data collectors, and statisticians are all blinded to group allocations. Besides, an independent researcher supervises the conversation between acupuncturists and physicians to avoid them communicating issues related to the allocation. Upon the culmination of 8 weeks intervention, patients will be asked to guess whether they perceived the insertion of the needle tip into their skin to assess the efficacy of blinding maintenance.

[figure not shown]

Figure 1: Flowchart of trial procedures

\*A: Daily Consumption of Methadone; B: Visual Analog Scale (VAS) for opioid craving;  
C: Clinical Opioid Withdrawal Scale (COWS); D: Beck Anxiety Inventory (BAI); E: Beck Depression Inventory II (BDI-II); F: Pittsburgh sleep quality index (PSQI)

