#### 4. Eligibility Criteria

##### 4.1 Inclusion Criteria

Patients will be included if they have:

- Diagnosed as opioid dependence according to the fifth edition of the Diagnostic and Statistical Manual of Mental Disorders (DSM-5) (Appendix 1) [44];
- Aged between 18-65 years;
- Received MMT for more than 6 weeks;
- Demand for methadone tapering;
- Not having received any kind of acupuncture therapy during the previous 3 months.

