## **4.2 Exclusion Criteria**

Patients will be excluded if they have:

- Serious heart, liver, lung, or kidney diseases;
- Syphilis or AIDS;
- Severe digestive disease or malnutrition;
- Severe primary hematological disorders;
- Received other treatment that may affect the efficacy evaluation of the present intervention;
- Infection, inflammation, scar, or injury close to the site of the selected acupoints;
- Pregnancy, or plans for pregnancy;
- Had a history of mental illness other than drug dependence.

In addition, all patients are instructed not to take any other medications aiming at alleviating withdrawal symptoms, improving sleep quality, or managing depression and anxiety during the study, in order to avoid initiating other interventions. Patients who consume such medications are excluded from the study.

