### **7.4 Analyses for Outcomes**

The analysis of proportion of participants with at least 20% reduction from baseline in the amount of methadone dose is performed using a generalized linear mixed model. For opioid craving VAS and all secondary outcomes, analysis is conducted utilizing a

linear mixed-model. For above models, values measured at baseline are used as covariates; intervention assignment, visit and intervention  $\times$  visit interaction are as fixed effects; and treatment centre and centre  $\times$  intervention interaction are as random effects. Before building the final model, we assess the poolability of treatment effects across centres by including centre  $\times$  intervention interaction in the model. If *P*-values corresponding to the interaction term for both primary endpoints are greater than 0.10, the treatment effect is homogenous across centres and centre  $\times$  intervention interaction will not be included in the final model. Primary outcomes use 2-sided tests at the 2.5% significance level. All other statistical tests are 2-sided at the 5% significance level. Dynamic data on the reduction in the methadone consumption and the opioid craving VAS score will be demonstrated in the figures, separated by two groups. Each row in the figures represents the reduction dose of the daily consumption of methadone (the opioid craving VAS score) for one participant. To investigate the relationship between daily consumption of methadone and the intensity of opioid craving over a 20-week period, scatter plots will be employed as a visual representation in this study with the x-axis representing the opioid craving VAS and the y-axis representing the methadone dose. The resulting scatter plot allows for the examination of the correlation between these two variables, providing insights into the potential influence of methadone intake on opioid craving levels over time.

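### Baseline urine opioid status is collected from everyone but is not named in the primary models, so some power is given up and any chance imbalance is left to post hoc handling

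*Combined protocol and SAP*

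**What the plan says.** Protocol section 7 provides for urine testing for opioids: "All participants will be asked to submit a urine sample at baseline, and randomly during the study each month, which are used to test for". It does not name the assay.

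Entry (protocol 4.1 and 4.2, repeated in SAP 3.2) requires, among other things, "Received MMT for more than 6 weeks" and "Demand for methadone tapering". No criterion mentions a urine result, abstinence or current use. The nearest exclusion, "Received other treatment that may affect the efficacy evaluation of the present intervention", concerns treatments.

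On randomisation, protocol 3.2 says "The randomization sequence is generated in the block size of 4" and names no stratification factor.

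For the models, SAP 7.4 (and protocol section 11) says "values measured at baseline are used as covariates; intervention assignment, visit and intervention" by visit enter as fixed effects, with centre and centre by intervention as random effects. No list of baseline values is given.

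Elsewhere, urine appears only as a secondary outcome (SAP 5.2). SAP 7.3 summarises and compares all baseline data by group. The only sensitivity analysis is per-protocol (SAP 7.5).

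**The concern.** A client with a positive baseline urine and one with a negative result are equally eligible. It is plausible that they differ on both primary outcomes. Appendix 2 ties methadone dosing to the severity of dependence and to control of craving, and protocol 2.1.2 links craving to relapse.

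If so, three things are at stake:

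- **Power.** The responder comparison loses some power by ignoring a predictor that is already in hand.
- **Imbalance.** The baseline table may show an imbalance, but no rule says what follows. Any adjustment would then be chosen after seeing the data.
- **Interpretation.** The SAP introduction sets the goal as lowering methadone while lowering relapse risk. A 20% reduction may mean something different in a client who also uses other opioids, and no planned display relates primary response to baseline urine status.

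The covariate phrase does not settle the matter. Its natural meaning is the baseline value of the outcome being modelled. If it means every baseline value, the covariate set is undefined.

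**Working it through.** **Inputs from the documents.** Response 70% versus 36%, 42 per group, 90% power at 5%, 50 per group after 15% attrition; craving difference 10 with SD 8 (protocol section 10). Primary tests are two-sided at 2.5% (SAP 7.4).

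**Inputs assumed.** Baseline urine positive in 30% to 50%; odds ratio for response, positive versus negative, of 1 (not prognostic), 0.4 or 0.2.

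**1. The plan's own figure.** The sum of variances is 0.70×0.30 + 0.36×0.64 = 0.4404 and the squared difference is 0.34² = 0.1156.

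- Unpooled: (1.960 + 1.282)² × 0.4404 / 0.1156 = 40.03, so 41 per group.
- Pooled: (1.960×√0.4982 + 1.282×√0.4404)² / 0.1156 = 43.2, so 44 per group.
- The stated 42 lies between these, and 42/0.85 = 49.4 gives 50.
- At the 2.5% level actually used, power is 82.5% with 42 per group and 89.2% with 50.

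**2. Chance imbalance, 50 per arm.** The SD of the between-arm difference in proportion positive is √(2p(1−p)/50): 0.092 at p = 0.3 and 0.100 at p = 0.5. Exact binomial probabilities:

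| Prevalence | Difference ≥ 10 points | Difference ≥ 20 points |
|---|---|---|
| 30% | 0.326 | 0.038 |
| 50% | 0.368 | 0.057 |

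**3. Effect of an imbalance on the result.** The shift in the risk difference is the imbalance times the gap in response between urine groups. With margins held at 70% and 36%, an odds ratio of 0.4 gives a gap of 19 to 21 points. A 10-point imbalance therefore shifts the result by 0.10 × 0.20 = 0.02, or 2 points. The standard error of the risk difference is √(0.4404/50) = 0.094, so the shift is 0.02/0.094 = 0.21 standard errors.

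**4. Responder power at the 2.5% level.** Simulated week-8 logistic comparison, likelihood-ratio test, 4,000 trials per scenario, without and with the urine covariate. Ranges cover 30% and 50% prevalence.

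| Odds ratio | 42 per arm: without → with | 50 per arm: without → with |
|---|---|---|
| 1 | 0.81–0.82 → 0.83 | 0.88–0.89 → 0.89–0.90 |
| 0.4 | 0.82 → 0.84–0.85 | 0.88–0.89 → 0.90–0.91 |
| 0.2 | 0.81 → 0.88 | 0.89 → 0.93–0.94 |

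These gains are about 2 to 3 points (0.4) and 4 to 7 points (0.2). Allowing for variation between simulation runs, 2 to 4 and 4 to 8 are fair ranges. A separate simulation under no treatment effect (50 per arm, prevalence 20% or 40%, odds ratios 1, 0.5 and 0.25) gave type I error of 2.1% to 2.8% with or without the covariate.

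**5. Craving.** With a difference of 10 and SD 8, power at 25 per group is 99.3% at the 5% level. On the plan's assumptions there is almost no power left to gain.

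**The case against.** The strongest case against is that this is a preference among covariates. Randomisation keeps the unadjusted test valid, and similar arguments could be made for baseline dose or time in treatment. SAP 7.3 would reveal an imbalance. Urine is reported as a secondary outcome. On the natural reading, the craving model already adjusts for baseline craving, which may carry part of the same information. At an odds ratio of 0.4 the gain is small, and a 2-point shift is minor beside a 34-point planned effect. Most of this stands and limits the size of the point. It does not answer the lack of a named covariate list or of a rule for handling an imbalance once seen.

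A reader might infer more than the documents support:

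- **That baseline urine is an established, strong prognostic factor.** No prevalence or association with either outcome is given.
- **That the result cleanly separates illicit users from abstinent clients.** The assay is unstated, every participant takes methadone (itself an opioid), and there is one baseline sample. Protocol 2.1.3 reports that an earlier trial in methadone clients lowered dose without raising positive opioid urines. This suggests a test that distinguishes other opioids, but the plan should say so.
- **That urine is certainly outside the models.** The covariate phrase is open, although the natural reading leaves urine out.

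**Conclusion.** The point holds as a modest matter of precision, pre-specification and interpretation. A baseline value taken from every participant is left out of entry and randomisation and is not named in the primary models. It would be wrong to conclude that the primary tests are biased or invalid, or that entry must be restricted: type I error is unaffected, and a chance imbalance is not bias on average.

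On the assumed prevalence of 30% to 50%, an imbalance of 10 points or more is common (33% to 37%), but one of 20 points or more is not (4% to 6%). The power gain for the responder outcome is worth having because 42 evaluable per arm gives only 82.5% at the 2.5% level. The gain depends entirely on an association that the documents do not supply, and it vanishes, without loss, if there is none. No gain is shown for craving.

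**What to change.** In protocol section 11 and SAP 7.4:

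1. Replace the general reference to baseline values with a named list of covariates for each model.
2. Include in that list, as a fixed covariate in both the dose-reduction generalised linear mixed model and the craving linear mixed model, the baseline urine result coded positive or negative for opioids other than methadone.
3. State the assay and what it detects in protocol section 7, so that the coding has a defined meaning.
4. Show both primary outcomes by baseline urine status and arm, descriptively and without tests. At 30% positive there would be only 0.30 × 50 = 15 positive participants per arm.

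The cost is wording. The sample is already planned for every participant, and entry criteria and sample size do not change. The list should be fixed before unblinding.

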## **8. Safety**

All participants will have some tests to check up on their bodies at screening and after 8-week intervention. Those tests are relative to the heart, liver, kidney, and other organs, including white blood cell count, hematocrit, hemoglobin, platelet, aspartate aminotransferase/alanine aminotransferase, blood urea nitrogen, creatinine, gamma-glutamyl transpeptidase, erythrocyte sedimentation rate and electrocardiogram.

Adverse events (AEs) are defined as events associated with acupuncture including fainting, hematoma, broken needle, infection, and bleeding. If any adverse events occur, these will be recorded by the acupuncturist and the treatment will be temporarily stopped. Every AEs will be fully recorded on the case report forms (CRFs) including all details of AEs. Serious AEs that threaten to participant's life or result in hospitalization will be reported to the Research Ethics Committee concerned within 24 hours.

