### **7.6 Safety Analyses**

All adverse events and serious adverse events will be listed. Adverse events include the acupuncture-related adverse events and other adverse events. Chi-square test or Fisher's exact test will be used to compare the incidence of adverse events between the manual acupuncture and sham control groups.

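### Protocol section 8 limits adverse events to those associated with acupuncture, recorded by unblinded staff, while SAP 7.6 also analyses other adverse events that no stated procedure collects

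*Combined protocol and SAP*

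**What the plan says.** Protocol section 8 gives the only definition of an adverse event: "Adverse events (AEs) are defined as events associated with acupuncture including fainting, hematoma, broken needle, infection, and bleeding". When such an event occurs, "these will be recorded by the acupuncturist and the treatment will be temporarily stopped". Serious AEs are introduced as those AEs that are life-threatening or "result in hospitalization will be reported to the Research Ethics Committee concerned within 24 hours". Protocol section 3.2 states that "acupuncturists are not blinded to group allocation".

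SAP 7.6 works with a wider set. It says "All adverse events and serious adverse events will be listed" and adds "Adverse events include the acupuncture-related adverse events and other adverse events". Incidence is then compared between arms by a chi-square or Fisher's exact test.

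The schedules (Protocol section 9, SAP section 4) mark AEs through the treatment phase and at weeks 12, 16 and 20. Section 8 also plans blood tests and an ECG: "All participants will have some tests to check up on their bodies at screening and after 8-week intervention".

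**The concern.** Safety is part of the stated aim in both documents (Protocol 2.2, SAP section 2). Participants enter because they want to taper methadone, and a dose reduction of at least 20% is a primary outcome. Appendix 2 foresees adverse reactions during dose reduction and asks the clinic physician to watch for them, but nothing routes what the physician sees to the AE record.

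A definition that requires a link to acupuncture places a causality judgement at the point of entry, and the only named recorder knows which needle was used. Events that do not pass that entry point cannot be compared between arms later. The SAP meanwhile promises a comparison that includes them. At stake is whether the reported AE and serious AE rates mean what a reader will take them to mean, and whether serious events unrelated to needling reach the ethics committee under the 24-hour rule.

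**Working it through.** The plan states no figure on this point, so the check is a comparison of texts.

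**1. The rules side by side**

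| Question | Protocol | SAP |
|---|---|---|
| What counts as an AE? | Section 8: events linked to acupuncture, with five needling examples | 7.6: acupuncture-related and other events |
| What counts as serious? | Section 8: a life-threatening AE, or one leading to hospital care | 7.6: listed, not defined |
| Who records? | Section 8: the acupuncturist | Not stated |
| Is the recorder blinded? | Section 3.2: no | Not stated |
| Who asks about other events? | Not stated | Not stated |
| Who judges relatedness? | Not stated | Not stated |
| Until when? | Section 9 schedule: week 20 | Section 4 schedule: week 20 |

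The first row is a contradiction: the SAP's second category is empty under the protocol's definition. The fifth and sixth rows are gaps in both documents.

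**2. Tracing one event.** Suppose a participant is admitted to hospital after an overdose in week 14, and nobody attributes it to needling.
- Protocol section 8: not associated with acupuncture, so not an AE. Serious AEs are a subset of AEs, so it is not a serious AE either, and the 24-hour report is not triggered.
- SAP 7.6: it belongs among the other AEs, should be listed, and should count in the test between arms.

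The same event is in the safety comparison under one document and outside it under the other.

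**3. Coverage over time.** Treatment lasts 8 weeks and follow-up 12, so 8 + 12 = 20 weeks. With 24 sessions in 8 weeks, the acupuncturist sees each participant on average 24 / 8 = 3 times a week. No sessions are planned in weeks 9 to 20, and no procedure says how AEs are collected at the marked weeks 12, 16 and 20.

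**4. What other data would show.**
- COWS at baseline and weeks 2, 4, 6, 8, 12, 16 and 20 (Protocol 6.2.1): "COWS evaluates common signs and symptoms of opioid withdrawal and monitors these symptoms over time".
- Craving VAS at the same visits; PSQI, BDI-II (with an item on suicidal thoughts) and BAI at baseline and weeks 4, 8, 12, 16 and 20.
- Urine tests for opioid use at baseline and at a random time each month (Protocol section 7), listed as a secondary outcome in SAP 5.2.
- Blood tests and ECG at screening and after week 8. SAP 7.6 names no analysis for them.

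These cover withdrawal, craving, mood, sleep, opioid use and organ function. None is designed to record a discrete event such as the week-14 admission.

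**5. Size.** The documents give no rate for events unrelated to acupuncture, so the number that would be lost cannot be calculated.

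**The case against.** The strongest reply is that harm is measured extensively. The repeated scales run to week 20 under independent research assistants rather than the acupuncturist, and opioid use is tested monthly. A reader might infer from section 8 that harms of tapering are not collected at all; step 4 of the working shows that this is wrong. What remains is the narrower gap for discrete clinical events.

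Second, a reader might infer that other AEs cannot be analysed. SAP 7.6 does plan the analysis, and the CRF, on which AE details are recorded, is not among the documents. One can say only that the plan states no basis for complete collection.

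Third, section 8 says that the acupuncturist records events, not that the acupuncturist judges cause. That is fair. The filter follows from the definition combined with the recorder: to record only associated events, someone must decide association, and no other role is named. Nor is the acupuncturist the only person who knows the allocation, since an independent researcher at the site performs it (Protocol 3.2).

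Fourth, some tempting figures do not measure the flaw:
- Weeks 9 to 20 are 12 / 20 = 60% of the observation period. That the acupuncturist's contact ends at week 8 is an inference, and a share of weeks is not a share of events.
- With 0 events among 50 participants, the one-sided 95% upper limit is 1 − 0.05^(1/50) = 5.8%. This depends only on arm size and is the same under any definition.
- Few haematomas or bleeds in the sham arm would reflect a real difference between penetrating and non-penetrating needles, not bias.

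Finally, Protocol 2.1.2 ties overdose deaths to tolerance and rising doses. It does not name overdose as a risk of dose reduction, and this point does not rest on that claim.

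**Conclusion.** The point stands in its limited form. The protocol and SAP define AEs differently, and following the protocol literally gives a safety comparison and a serious-event report that leave out clinical events not attributed to acupuncture. This is a conflict between two rules, not just missing detail. In addition, no procedure is stated for asking about such events or judging relatedness at any time in the 20 weeks, and unblinded staff would in effect filter relatedness at entry. The direction of any resulting bias cannot be determined from the documents.

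The conclusion assumes that section 8 is applied as worded and that the CRF or site procedures do not already collect all-cause events. If they do, the remedy is to bring section 8 into line with them. Neither primary outcome is affected. The documents do not support the wider conclusions that tapering harms go unmeasured or that the comparison in SAP 7.6 is impossible.

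**What to change.** **Protocol section 8.** Define an AE as any untoward medical occurrence from randomisation to week 20, regardless of cause, and apply the serious-event definition and the 24-hour report to all of these.

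**Collection.** Have the research assistants who run the assessments ask one standard, open question at weeks 2, 4, 6, 8, 12, 16 and 20. Protocol 3.2 lists outcome assessors and data collectors as blinded; state explicitly that this covers these assistants. The acupuncturist continues to log needling reactions at treatment sessions, which keeps the existing AE schedule, including weeks 3, 5 and 7. Name the role that judges relatedness, preferably blinded to allocation.

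**SAP 7.6.** Use the same definition. Report needling reactions separately from all other AEs and from serious AEs. Opioid use found by urine test stays a secondary outcome and need not be recoded as an AE.

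**To reconcile.** Section 8 ties a temporary stop of treatment to any AE. Under a wider definition that sentence would reach events for which it may not have been intended, so the sponsor must reconcile the two.

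**Cost.** Protocol, SAP and CRF wording, one added question per visit and more events to list. No extra staff or visits are needed.

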|                  | Daily Consumption of Methadone | ×          |                                                                                      | × |   | × |   | × |   | × | ×         | ×  | ×  |
|                  | opioid craving VAS             | ×          |                                                                                      | × |   | × |   | × |   | × | ×         | ×  | ×  |
|                  | COWS                           | ×          |                                                                                      | × |   | × |   | × |   | × | ×         | ×  | ×  |
|                  | BAI                            | ×          |                                                                                      |   |   | × |   |   |   | × | ×         | ×  | ×  |
|                  | BDI-II                         | ×          |                                                                                      |   |   | × |   |   |   | × | ×         | ×  | ×  |
|                  | PSQI                           | ×          |                                                                                      |   |   | × |   |   |   | × | ×         | ×  | ×  |
|                  | ADVERSE EVENTS:                |            |                                                                                      | × | × | × | × | × | × | × | ×         | ×  | ×  |

Figure 4: Schedule of enrolment, interventions, and assessments

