To investigate the relationship between daily consumption of methadone and the intensity of opioid craving over a 20-week period, scatter plots are employed as a visual representation in this study with the x-axis representing the opioid craving VAS and the y-axis representing the daily consumption of methadone. The resulting scatter plot allows for the examination of the correlation between these two variables, providing insights into the potential influence of methadone intake on opioid craving levels over time.

Efficacy analyses will be performed for both the full analysis set (FAS) population and the per-protocol set (PPs) population. The FAS population will consist of all randomized patients who received at least one treatment. In a PPs analysis, only patients who complete all the clinical trials according to the protocol are counted towards the results. Besides, the PPs population in our research will meet these criteria: the experimental treatment requirements; the main variables can be determined; no missing baseline variables; no major violation of the test scheme. Safety analyses will be performed on the safety population, which will be comprised of all randomized subjects who have been administered at least one treatment. A PP analysis is carried out as a sensitivity analysis compared with the results obtained using the FAS analysis. When the PPs and FAS analysis conclusions are not the same, it is necessary to analyze the possible reasons and discuss them.

Primary outcomes used 2-sided tests at the 2.5% significance level. All other statistical tests are 2-sided at the 5% significance level.

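### Protocol section 8 limits adverse events to those associated with acupuncture, so the other events that SAP 7.6 lists and compares are not clearly collected or reported

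*Combined protocol and SAP*

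**What the plan says.** Protocol section 8 gives the definition: "Adverse events (AEs) are defined as events associated with acupuncture including fainting, hematoma, broken needle, infection, and bleeding". When such an event occurs, "these will be recorded by the acupuncturist and the treatment will be temporarily stopped", with details entered on the case report form. Serious adverse events that threaten life or "result in hospitalization will be reported to the Research Ethics Committee concerned within 24 hours". Section 3.2 says that "acupuncturists are not blinded to group allocation", while outcome assessors and data collectors are.

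SAP 7.6 takes a wider view: "Adverse events include the acupuncture-related adverse events and other adverse events". All adverse and serious adverse events are to be listed, and a chi-square or Fisher's exact test "will be used to compare the incidence of adverse events between the manual acupuncture and sham control groups". The safety population in protocol section 11 is "comprised of all randomized subjects who have been administered at least one treatment".

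The row labelled "ADVERSE EVENTS" in protocol Figure 4, repeated in SAP section 4, is marked at weeks 2 to 8 and at weeks 12, 16 and 20. Section 3.1 sets 8 weeks of treatment and 12 weeks of follow-up.

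**The concern.** A SAP can analyse only what the protocol has someone collect. Section 8 builds attribution to acupuncture into the definition, so the judgement of relatedness comes before recording rather than after it, and the only named recorder knows the arm. Events outside the definition have no stated route to the case report form, although SAP 7.6 expects to list them and include them in a between-arm test.

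The events at risk of being missed matter in this trial. Participants are tapering methadone, and safety is a stated aim. Protocol section 2.1 itself discusses overdose deaths, cardiac rhythm effects and relapse. A sparse count of other events could reflect the collection rule rather than their absence. A hospital stay judged unrelated to needling might also not prompt the 24-hour report.

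**Working it through.** The plan states no figure to reproduce, and the point needs no power or alpha calculation. The check compares the texts and counts the schedule marks.

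**1. Scope of the definition.** In section 8 the word before the five examples makes them illustrative, so other acupuncture-associated events are covered. It does not extend the definition to events that are not associated with acupuncture. SAP 7.6 has two classes, acupuncture-related and other. Section 8 covers the first only.

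**2. Serious events.** Section 8 describes them as serious AEs, a subset of the term it has just defined. Read literally, the 24-hour report carries the same limit.

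**3. A worked case.** Suppose a participant is hospitalized in week 6 after an overdose and the acupuncturist judges it unrelated to needling.
- Under section 8 it is not an adverse event. No entry is required, and the 24-hour report is not triggered.
- Under SAP 7.6 it is an other adverse event and a serious one, to be listed and counted.
- If it happens in week 14, it falls between the week 12 and week 16 visits, and no one is named to ask about it or record it.

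**4. Schedule count.** Marks: weeks 2, 3, 4, 5, 6, 7, 8, 12, 16, 20 = 10. Marks after week 8: weeks 12, 16, 20 = 3, so 3/10 = 30%. The blank week 1 cell may come from reading the table out of PDF; if so, the count is 3 of 11. Follow-up after acupuncture is 12 of 20 weeks = 60%. These figures describe the schedule. They do not measure harm or uncollected events.

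**5. Effect on the SAP 7.6 comparison.** The denominator is everyone treated at least once. On the literal reading, the numerator is only those events that an unblinded recorder has attributed to acupuncture. The documents do not allow the direction of any resulting bias to be stated.

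**6. What is collected whatever the cause.** Laboratory tests and ECG at screening and after week 8 (section 8); COWS at weeks 2, 4, 6, 8, 12, 16 and 20, seven post-baseline visits (section 6.2.1); monthly urine tests (section 7); sleep, depression and anxiety scales to week 20 (section 6.2); daily attendance for methadone (section 6.1.1); and monitoring by the clinic physician, who can stop the taper (Appendix 2). None of these widens the definition, names a recorder for follow-up, or sends a hospitalization or overdose to the adverse event record.

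**7. BDI-II item 9 (secondary).** Appendix 7 asks about suicidal thoughts. Section 6.2.3 gives the form at baseline and weeks 4, 8, 12, 16 and 20, so 6 times, 3 of them after acupuncture ends. It is scored as a sum to 63, of which item 9 contributes at most 3 (3/63 = 4.8%), so the total does not reveal the answer. Research assistants supervise the paper form (section 6.2.4). No visible text requires anyone to act on a non-zero answer.

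**The case against.** The strongest reply is that section 8 should not be read alone. The same combined document schedules adverse events to week 20, which makes little sense for needling events only, and SAP 7.6 says outright that other events count. Read together, the plan shows an intention to capture all causes, and the defect is one unharmonized sentence plus an unnamed recorder. The cause-neutral measures are also substantial, and blinded assessors collect many of them, so the acupuncturist is not the only source of harm data.

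Much of this stands. A reader might infer that no other events will be collected, or that safety goes unobserved after week 8. The documents do not support that: the visits are scheduled, the SAP intends the wider class, and withdrawal, opioid use, laboratory values and ECG are measured regardless of cause. What remains is that intention in a SAP does not instruct site staff. The operative rule in section 8 is narrower, and spontaneous events such as hospitalization fall outside the other measures.

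A reader might also infer that suicidal answers would be ignored. That does not follow either. The case report form, the acupuncturists' brochure and site procedures cannot be seen and may cover it. Section 4.2 excludes a history of other mental illness, and patients are seen daily.

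**Conclusion.** The point holds as an inconsistency with a practical consequence: followed as written, section 8 would under-collect what SAP 7.6 reports, and it leaves serious events judged unrelated to needling outside the literal scope of the 24-hour report. For the three follow-up visits no recorder is named. The change should be made, but it does not threaten the trial's main result: primary efficacy inference is unaffected.

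The number of missed events cannot be given, because the documents contain no event rate. The conclusion assumes that sites apply section 8 literally and that the unseen case report form does not already ask about all causes. If it does, the remaining task is to align the wording. The item 9 point rests on absence from the visible text and carries lower confidence.

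**What to change.** **Section 8.**
- Define an adverse event as any untoward event regardless of cause, with acupuncture-related events as a marked subset, to match SAP 7.6.
- Apply the 24-hour serious event report to all causes.
- Keep the temporary treatment stop for acupuncture-related events only.
- Have the blinded research assistants ask one open question about other events at each scheduled visit, including weeks 12, 16 and 20, after the craving VAS and the other scales are completed.
- Leave needle-site events with the acupuncturist through week 8, and name a person not involved in outcome assessment to record late ones. The recorder of needle-site events stays unblinded; that is the price of keeping bruising and bleeding away from the blinded assistants.

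**BDI-II item 9 (sections 6.2.3 and 8), unless the case report form or site procedures already cover it.** The assistant reads item 9 before the participant leaves, and any non-zero answer goes the same day to a clinician who is not told the allocation. Someone other than the methadone prescriber is preferable, because an alert could slow the taper and so touch the dose-reduction outcome. If medication started as a result is not to end follow-up, protocol section 4.2 and SAP section 3.2.2 must be amended too, since both now exclude patients who take medication for depression or anxiety.

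**Cost.** A short amendment, one case report form line for other events and one for item 9, using existing staff and visits. Expect a few extra minutes per visit, more minor events to record, some item 9 alerts that need no action, and a small risk that a participant mentions bruising or bleeding to a blinded assistant. Asking after the scales are done protects that visit's scores, though not those at later visits.
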